#### Control group

Patients will receive enteral feeding at the discretion of the leading physician. Feeding practice differs between staff and usually relies on an increase of enteral feeding by 5–20ml/kg/day. Subjective evaluation of feeding tolerance, will be defined as one of the following: bilious or milk residuals, distended abdomen, and vomiting. Withholding or slowing down feeding will be subject to an induvial decision of the attending.

#### Study group

To meet the nutritional goals, infants will receive enteral feeding based on the following protocol (14):

Minimal enteral nutrition (MEN) will begin within 72 h life at 10 to 20 mL/kg/day, breast milk/donor human milk. MEN will not be included in the caloric goals.Advancements in feeding will be set at 20–30 mL/kg/day, but not more than 10 ml per feeding portion to reach a goal of 150 ml/kg/day, but not more than 120ml/kg/day in cases of fluid restriction).The goal will be to reach an overall daily caloric intake of minimum 100 kcal/kg/d.

In both groups the interventions will continue up to 28 days of life or day of cardiosurgical treatment, whichever comes first.

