### Trial design

Parents of the neonates born after 36 weeks of pregnancy with duct-dependent CHD will be offered participation in the study within the first 3 days of life. After provision of oral and written information about the study, both parents will be asked to sign a written consent for their child to participate in the study (Table 1).

**Table 1 T1:** Study timetable.

**Timepoint (state unit)**	**T0**	**T1**	**T2**	**T3**	**T4**	**T5**	**T6**	**T7**

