#### Eligibility criteria

All parents of infants diagnosed with a duct dependant lesion and admitted to participating units will be approached by one of the research team members within the first 72 h of life (as full enteral feeding is usually reached at a minimum of 7 days of life). He or she will explain the study and obtain written consent for participating in the trail. Recruitment will take place between June 1st 2022 and June 30st 2024. After obtaining written consent for participating in the trial, the patient's medical record number (MRN) will be immediately registered on REDCap (Research Electronic Data Capture). Patients eligible for the trial must comply with all the following **at randomization**.

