#### Exclusion criteria

1. Potential contradictions to early central feeding; neonates with gastrointestinal anatomic and maxillofacial abnormalities.2. Feeding intolerance defined as vomiting bile or haemorrhagic residuals (23).3. Hemodynamic instability defined as hypotension requiring at least two inotropes for at least 72 h.4. > 50% formula based enteral feeding Studies have shown that infants with duct dependent CHD, who were fed with a predominately human milk-based diet have a lower risk of NEC.5. Birth weight <2500 g In a large multi-center cohort of patients with HLHS, El-Hassan et al. failed to show an increased risk of NEC, but outcomes were worse in the group of babies with low birth weight (24).

Optimal nutrition is crucial to improve short- and long-term outcomes in newborns with CHD. However, large, well designed randomized controlled studies are not available, hence feeding practices differ between units and physicians. Furthermore, a position statement regarding nutritional support for children with critical illnesses (including CHD) is based on studies in preterm populations (13). Given the above, selecting a physician led enteral feeding regime as a comparator is therefore justified.

Patients will be randomized to either the physician led enteral feeding (control group) or protocol-based feeding group (study group).

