### Assignment of interventions

#### Allocation (sequence generation, concealment mechanism and implementation)

A member of the recruitment team will approach caregivers within the infant's first 72 h of life. He or she will explain the study and obtain written consent for participating in the trail. Infants who fulfill inclusion criteria will be randomized.

A study number together with the allocated treatment will be assigned by REDCap. The allocation sequence will be computer-generated. Patient's data along with the result of the allocation will be sent to statistical team. Block randomization with stratification by type of lesion (ductal dependent pulmonary, systematic, or mixing blood flow) will be implemented. Patients will be randomly assigned to standard or physician-led enteral nutrition guidelines in 1:1 ratio. To ensure allocation concealment, the randomization list will remain with the statistical team for the whole duration of the study. The block size will be variable and concealed until primary endpoint analyses.

Thus, randomization will be conducted without any influence of the principal investigators, clinicians, recruitment or follow up staff.

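### The deadline for starting study-arm feeds is also the latest time a family may be approached, so a validly randomised late entrant can miss the start rule in one arm only, under a per-protocol primary analysis

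*Protocol article*

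**What the plan says.** Five parts of the protocol article bear on the timing of entry and first feed.

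- **Study group:** "Minimal enteral nutrition (MEN) will begin within 72 h life at 10 to 20 mL/kg/day". The clock runs from birth, not from randomisation.
- **Eligibility criteria:** parents "will be approached by one of the research team members within the first 72 h of life". The section on allocation repeats this: "A member of the recruitment team will approach caregivers within the infant's first 72 h of life". Trial design puts it in days: parents "will be offered participation in the study within the first 3 days of life".
- **Steps after the approach:** under Trial design, "both parents will be asked to sign a written consent for their child to participate in the study". Eligibility is judged at randomisation ("Patients eligible for the trial must comply with all the following"), and allocation follows: "Infants who fulfill inclusion criteria will be randomized". No latest hour for randomisation is given.
- **Table 1 and Participant timeline:** screening, consent and allocation all fall at T0, defined as the first day of life.
- **Control group:** feeding is left to the treating physician's judgement, with no start time.

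Two further sections determine the consequence. Statistical methods makes the per-protocol set primary for all outcomes. Interim analyses makes intention-to-treat a sensitivity analysis and has a blinded committee decide, from protocol deviations, which population a patient belongs to.

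**The concern.** The same 72 h serves both as the outer limit for first contact with a family and as the deadline for an action that can only be prompted by allocation, several steps later. The two fit together for early entrants but not at the late end of the window. There, an infant can satisfy every entry rule and still be outside the study-arm feeding rule on the day of allocation.

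The mismatch falls on one arm, because only the study arm has a start deadline. Under an intention-to-treat primary analysis this would be an adherence detail. Under a per-protocol primary analysis it can decide who is counted. If late-entered study infants are set aside while comparable late-entered controls stay, the arms no longer match on time of diagnosis or transfer, or on whatever prognosis goes with it.

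**Working it through.** **1. The windows side by side**

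| Event | Limit stated | Section |
|---|---|---|
| First approach to family | up to 72 h of life (or first 3 days) | Eligibility criteria; Allocation; Trial design |
| Consent, eligibility check, randomisation | after approach; no latest hour | Trial design; Eligibility criteria; Allocation |
| Screening, consent, allocation | day 1 | Table 1; Participant timeline |
| First feed, study arm | by 72 h of life | Study group |
| First feed, control arm | none | Control group |

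Time left for a family approached at the last permitted moment: 72 h − 72 h = 0 h for consent, eligibility check, allocation and first feed. If Table 1 governs instead, allocation on day 1 leaves about two days before the deadline. The two schedules cannot both describe enrolment.

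**2. Who is affected.** Only a study-arm infant who is (a) randomised after, or too close to, 72 h and (b) not already on feeds that satisfy the rule. An infant already given human milk under routine care at the stated volume complies, whenever randomised.

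**3. A related timing problem.** One exclusion criterion reads "Hemodynamic instability defined as hypotension requiring at least two inotropes for at least 72 h". It cannot be met before about 72 h of life, yet eligibility is judged at randomisation. This does not show that randomisation must wait. It does show that the entry clock was not aligned with the criteria applied at entry.

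**4. Illustrative size of the bias.** The documents give no distribution of enrolment times, so the inputs f and r below are assumptions.

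- p = 18%, the control-arm NEC incidence in the Sample size section, applied to both arms (no true effect).
- f = share of the study arm removed from the per-protocol set for a late start.
- r = NEC risk of the removed infants relative to the remainder.

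Risk among the study infants who remain = p / [(1 − f) + f·r]. Bias (study minus control) = that value − p.

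| f | r = 0.5 | r = 1 | r = 2 |
|---|---|---|---|
| 5% | 0.18/0.975 = 18.46%, +0.46 points | 0 | 0.18/1.05 = 17.14%, −0.86 points |
| 10% | 0.18/0.95 = 18.95%, +0.95 points | 0 | 0.18/1.10 = 16.36%, −1.64 points |
| 20% | 0.18/0.90 = 20.00%, +2.00 points | 0 | 0.18/1.20 = 15.00%, −3.00 points |

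For scale, the design difference is 18 − 7.6 = 10.4 percentage points. A negative shift favours the study arm. There is no bias if late entrants carry the same risk as the others (r = 1), and none if they are not removed.

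**The case against.** The case against is substantial, and much of it stands.

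- **Most infants are probably enrolled early.** Recruitment describes an offer at the antenatal cardiology consult and a second screen at intensive care admission. Study setting describes referral centres for fetuses with CHD, and Table 1 places allocation on day 1. A reader might put a figure on the share who miss the deadline by assuming approaches spread evenly over 72 h plus a fixed delay. The documents support neither assumption, so no such share is claimed.
- **Power.** A reader might infer that the study arm loses power. Recruitment says enrolment continues until at least 192 valid observations are held in each arm. If excluded infants do not count as valid, which is the natural reading, they are replaced. Loss of power is not part of this point. Replacement does not undo selection, however.
- **Late start is not stated to mean exclusion.** A reader might infer that late infants will be dropped. No text says so. Deviations go to blinded review, and the detailed definition of the per-protocol set may sit in an analysis plan that is not shown; its absence is not the complaint. Blinding protects less here than usual, though: only one arm has a start deadline, so a late-start deviation reveals the arm.
- **The larger issue is per-protocol as primary in a superiority trial.** That is a separate matter. It is what gives this timing conflict its consequence, but the conflict is in the text either way.
- **A start rule in one arm is inherent in the comparison.** True. The asymmetry meant here concerns that rule alone; controls can deviate in other ways.

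**Conclusion.** The point holds in a limited form. As written, the approach window, the day-1 allocation and the study-arm feeding deadline cannot all apply. A properly randomised study infant can be outside the start rule at allocation, with no counterpart among controls. With a per-protocol primary analysis and set membership decided from deviations, this could remove infants from one arm only and bias the comparison.

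How many infants are affected is not stated and may be few. In the illustration, removing 5% to 20% of the study arm shifts the risk difference by between +2.00 and −3.00 percentage points. That rests on no true effect, 18% risk, removed infants at half to twice the risk of the rest, and actual exclusion of late starters. The direction cannot be predicted from the documents. The bias is modest beside the design difference of 10.4 points and avoidable, so the text should be corrected; it does not show that the trial will fail.

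**What to change.** Two changes of wording:

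1. Reconcile Trial design, Eligibility criteria, Study group, the Allocation section and Table 1 with the Participant timeline on one clock, so that every infant who may be randomised can meet the study-arm start rule as written. The timing of the inotrope exclusion should be checked in the same pass. The start time itself is for the investigators to decide; none is proposed here.
2. State that an infant randomised too late to meet the start rule is not excluded from the primary analysis for that reason. If the first change is complete this will rarely be needed, but it settles any remaining case before outcomes are known.

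The cost is an amendment, with no new procedure or data item. Depending on how the clocks are aligned, either a few late-approached families are not randomised or the wording of the deadline changes.

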### Criteria for modifying or discontinuing allocated interventions

In infants who present with *one or two* of the following symptoms such abdominal distention, visible bowels loops or feeding intolerance (defined as emesis ≥2 consecutive feeds, or gastric residuals of >50% per feed in ≥2 consecutive feeds, bilious residuals, bilious emesis) the intervention will be **modified** by decreasing enteral nutrition by 50% and substituting the remaining fluid requirements with adequate parenteral nutrition for a **maximum** of 48 h. If symptoms persist above 48 h, the trial will be discontinued.

The trial will be **discontinued** if the following occur:

The patient presents with at least three of the following symptoms.

Abdominal distention.Visible bowels loops.Feeding intolerance (defined as emesis ≥2 consecutive feeds, or gastric residuals of >50% per feed in ≥2 consecutive feeds, bilious residuals, bilious emesis)..Temperature instability (defined as ≥2 consecutive measurements).Presence of bowel perforation of NEC confirmed on abdominal x-ray or ultrasound.

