#### Primary outcome

Patients will be evaluated for NEC based on the presence of at least three of the following clinical symptoms (37–40).

Abdominal distention.Visible bowels loops.Feeding intolerance (defined as emesis ≥2 consecutive feeds, or gastric residuals of >50% per feed in ≥2 consecutive feeds, bilious residuals, bilious emesis).Temperature instability (defined as ≥2 consecutive measurements).Frank bloody stools.Cardiovascular instability (hypotension; defined as MAP <30 mmHg, tachycardia >160/' or bradycardia <80/').Recurrent apnoea.Increase of abdominal girth > 2 cm (allowing inter-observer variability of 1 cm) within 12 hAbdominal wall erythema.

And/or at least 2 of the below laboratory findings based on Walsh and Bell criteria (modified by Kliegman) (25, 37).

Thrombocytopenia < 50 kLeukopenia <6 kCRP > 10 mg/dlPCT > 1 IU/lCoagulopathy.

NEC will be diagnosed using the abdominal ultrasonography (AUS) or plain abdominal radiography (AR).

Gray- scale AUS will be used to assess bowel wall echogenicity, measure bowel wall thickness, peristalsis, pneumatosis intestinalis (PI), portal vein gas (PVG), free abdominal air and fluid. The following finding on AUS will be equivalent do NEC (41):

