### Statistical methods

#### Statistical methods for primary and secondary outcomes

As the trial is designed as a superiority study, both primary and secondary outcomes will be analyzed based on the per-protocol (PP) approach.

For primary outcomes and dichotomous secondary outcomes, between-group differences, and the two-sided 95% confidence interval (CI) for the estimated difference approach will be used (47–49).

For continuous outcomes, means/medians and 95% CIs will be calculated. Differences in changes from baseline between treatment groups will be compared using a two-sample t test or Mann-Whitney *U*-test (50).

Additionally, a predictive model to clarify the risk of NEC complications in both study groups will be implemented. Statistical and machine learning techniques such as decision trees, random forests, and support vector machine (SVM) will be used (51–55).

All statistical calculation will be carried out using R package (The R Foundation Vienna, Austria) and Statsoft (Hamburg, Germany).

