#### Interim analyses

Our study is a multicentre study, located in 4 different unit. Three interim analyses (IA) will be performed on the primary end point every 100 recruited patients. IA will be conducted by an independent statistician, blinded for the treatment allocation. This will allow us to track trial data collected on case report forms and generate performance metrics. Additionally, it will make data and study information available in a timely manner and re-estimate the sample size if needed. Results of interim analyses will be reported to the DMC, which will decide whether the trial should be continued or stopped for futility based on the pre-specified criteria. The Peto approach will be used: the trial will be ended using symmetric stopping boundaries at *P* < 0.001 (56).

Additionally, sensitivity analysis for the primary outcomes will be carried out with an intention-to-treat (ITT) approach. Protocol deviations will be reviewed by a blinded adjudication DMC who will decide by consensus whether a patient should be included in the ITT or per protocol population. We do not plan any subgroup analyses. In case of missing data, standard data imputation algorithms will be used (e.g., multiple imputation) (55).

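### The study arm's feed-reduction and stopping rules do not match the trigger for NEC evaluation, so some infants under work-up have no clearly stated feeding action until imaging is read

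*Protocol article*

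**What the plan says.** Four sections of the protocol article bear on the point.

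- *Study group* fixes the pace of feeding in the intervention arm: "Advancements in feeding will be set at 20–30 mL/kg/day". It gives no exception for an infant with suspected NEC.
- *Control group* leaves the matter to judgement: "Withholding or slowing down feeding will be subject to an induvial decision of the attending".
- *Criteria for modifying or discontinuing allocated interventions* contains two rules. Enteral feeds are halved for at most 48 hours when one or two signs are present, the signs being introduced as "following symptoms such abdominal distention, visible bowels loops or feeding intolerance". The intervention stops if those signs last beyond 48 hours, or under this condition: "The patient presents with at least three of the following symptoms". The list that follows adds temperature instability and imaging-confirmed perforation or NEC to the three abdominal signs.
- *Primary outcome*, under the plans for data collection, says when to look for the endpoint: "Patients will be evaluated for NEC based on the presence of at least three of the following clinical symptoms". Nine signs follow. There is also a laboratory route, "And/or at least 2 of the below laboratory findings based on Walsh and Bell criteria". Diagnosis then rests on abdominal ultrasound or radiography.

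**The concern.** The trial asks whether faster enteral feeding is safe with respect to NEC. The criteria section is where the article says when feeding must slow or stop. If the signs that send an infant for NEC imaging are not the signs that slow feeding, an infant can be under investigation for NEC while the written regimen still calls for feeds to rise.

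The omitted signs are not incidental by the article's own account. Its background cites a study in which low cardiac output and shock were associated with NEC (odds ratio 6.5, 95% CI 1.8–23.5). Cardiovascular instability is one of the nine evaluation signs, yet it prompts no feeding action.

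The gap affects the study arm only. In the control arm the attending may withhold feeds at any time. What is at stake is the safety of study-arm infants between trigger and imaging result, and the clarity of the instruction given to the staff caring for them.

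**Working it through.** The plan gives no figure to reproduce, so the check is a comparison of the two lists followed by a count of combinations.

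**Step 1: the lists side by side.**

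| Sign that counts towards NEC evaluation | In the reduction rule | In the stopping list |
|---|---|---|
| Abdominal distension | yes | yes |
| Visible bowel loops | yes | yes |
| Feeding intolerance | yes | yes |
| Temperature instability | no | yes |
| Frank bloody stools | no | no |
| Cardiovascular instability | no | no |
| Recurrent apnoea | no | no |
| Girth increase > 2 cm | only if read as distension | only if read as distension |
| Abdominal wall erythema | no | no |

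**Step 2: the rules as applied before imaging.** Stop if at least three of distension, loops, intolerance and temperature instability are present. Otherwise reduce if at least one of distension, loops or intolerance is present. Otherwise no action is stated. This takes the reduction list as closed.

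**Step 3: minimal triggers, exactly three of nine signs.** The total is C(9,3) = 84.

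- Girth as a separate sign: stop C(4,3) = 4. No action when all three signs come from the six outside the abdominal group, C(6,3) = 20. Reduce 84 − 4 − 20 = 60.
- Girth counted as distension: stop 7 (the four above, plus three in which girth stands in for distension). No action C(5,3) = 10. Reduce 84 − 7 − 10 = 67.

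**Step 4: all sets of three or more signs.** The total is 2⁹ − 1 − 9 − 36 = 466.

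- Girth separate: no action in 2⁶ − 1 − 6 − 15 = 42, and 42/466 = 9.0%.
- Girth as distension: no action in 2⁵ − 1 − 5 − 10 = 16, and 16/466 = 3.4%.

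Bloody stools with recurrent apnoea and wall erythema is uncovered on either reading of girth.

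**Step 5: after imaging confirms NEC.** If the last item of the stopping list stands alone, the uncovered count falls to 0. If it is only one item towards the three, as printed, the same 20 (or 10) minimal triggers stay uncovered. Such an infant can have at most two items on the stopping list: temperature instability and the confirmed diagnosis.

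**The case against.** The best defence is that the two lists serve different purposes. One says when to look for NEC and can afford to be sensitive; the other says when to change feeding. These infants often have cardiac and respiratory failure, and the cardiovascular item includes a heart rate above 160, which may have nothing to do with the gut. Tying feed changes to abdominal signs is a defensible choice, and a broader rule would add interruptions in the arm meant to advance. This supports leaving isolated signs out of the feeding rules. It is weaker once three signs together have already prompted a NEC work-up, when a short pause until imaging is read is a modest precaution.

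A second defence is the wording. The sentence introducing the reduction rule is broken; if the word *as* has dropped out after *such*, the list is illustrative. The action for other signs is then unclear rather than absent, which is why the point is put that way here. Nothing forbids a clinician from holding feeds. The flowchart and the full protocol, which are not shown, may say more, but the article prints both lists and they disagree.

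Three stronger readings are tempting, and the documents do not support them.

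- *That 20 of 84 (24%) describes how many infants are exposed.* The count weights every combination equally, assumes a closed list and treats a measured girth increase as something other than distension. The article gives no frequency for these presentations.
- *That the gap biases the primary analysis.* The article states that "both primary and secondary outcomes will be analyzed based on the per-protocol (PP) approach", so a reader might infer that a prudent hold would remove study-arm infants with NEC from the analysis while the same hold in a control is compliant. No section calls such a hold a deviation. Of deviations in general it says "Protocol deviations will be reviewed by a blinded adjudication DMC who will decide by consensus", and an intention-to-treat sensitivity analysis is planned. Interrupted feedings are themselves a secondary outcome. The Stage II and III definitions require a distended abdomen, so an infant who reaches the endpoint will usually have acquired a sign that permits reduction. Arm-specific exclusion is a possible side effect, and no size can be put on it.
- *That feeding continues after NEC is confirmed.* The printed layout says so literally, but a lost list level is the likelier explanation.

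**Conclusion.** The mismatch is real and should be corrected. A study-arm infant with three or more evaluation signs but no distension, visible loops or feeding intolerance has no clearly stated feeding action between trigger and imaging result, while the regimen sets a daily advance.

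In terms of rule coverage, 10 of 84 minimal triggers are uncovered when girth increase is read as distension, and 20 of 84 when it is not. Both figures rest on a closed reduction list and say nothing about how often such infants occur. The window probably ends when imaging confirms NEC, provided that item was meant to stand alone.

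The case rests on patient safety and clear instruction, not on bias in the estimate. It is confined to the clinical trigger in the study arm. The criteria section names no laboratory findings either, but that is a lesser matter because they may reflect sepsis.

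**What to change.** Add to the criteria section, and to the flowchart described under *Strategies to improve adherence to interventions*, a rule to this effect: any study-arm infant who meets the clinical trigger for NEC evaluation has feeds held, or at least not advanced, until imaging is read; this is protocol-compliant; and where the existing reduction or stopping rule also applies, the stricter action is taken. Print imaging-confirmed NEC or perforation as a stand-alone reason to stop, outside the count of three. Leave control-arm discretion as it is.

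The cost is a short amendment, with no added patients or tests, since the evaluation is already planned. The downside is some additional feed interruptions in the study arm. These would affect three secondary outcomes: interrupted feedings, protein and caloric intake, and days to full enteral feeding. Their number cannot be estimated from the article.
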